### Quality Control

In order to reduce potential errors and ensure the quality of the trial, all acupuncturists and evaluators must receive professional training before the trial. The training course includes the recruitment, intervention, and evaluation processes. The integrity and accuracy of the data will be monitored by clinical trial experts from the clinical research center of the First Affiliated Hospital of traditional Chinese medicine of Henan University. All clinical trial experts are independent of the subject principle. In addition, we will set up a quality control group to supervise whether the experimental procedures comply with the standard guidelines. When the total number of samples collected reaches 54, statistical analysis will be carried out. The lead investigator will obtain these interim results and decide whether to continue the trial. If the efficacy of the experimental group is lower than that of the other two groups in the results of interim data, we will stop the trial.

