## Methods and Analysis

### Trial Design and Setting

This was a parallel design and randomized controlled trial. The subjects were be recruited from the Rehabilitation Center of the First Affiliated Hospital of Henan University of Chinese medicine. We selected 108 patients who met the predefined criteria and randomly divided them into 2 groups, with 54 patients in each group: the experimental group and the control group. All patients received 20 courses of treatment for 4 weeks, and the upper limb function was evaluated before and after treatment. The efficacy of the experimental group when compared with the control group was analyzed after data collection. An example template for the content of admission plans, interventions, and evaluations is shown in Table 1. Our protocol presentation is in accordance with the Standard Protocol Items: Recommendations for Interventional Trials 2013 (SPIRIT 2013) guidelines (30). The study flowchart is presented in Figure 1.

**Table 1 T1:** Qualification screening and informed consent was completed before the assignment.

**Timepoint**	**Enrollment**	**Allocation**	**Treatment period**			
	**−1 week**	**0 week**	**1 week**	**2 week**	**3 week**	**4 week**
Enrollment						
Eligibility screen	X					
Baseline	X					
Informed consent	X					
Medical history	X					
Merger disease	X					
Allocation		X				
Interventions						
Experiment group			X	X	X	X
Control group			X	X	X	X
Assessments						
MAS		X				X
FMA-UE		X				X
CSS		X				X
MBI		X				X
Safety evaluation		X				X
Needle sensation			X	X	X	X
Adverse events			X	X	X	X

*After allocation, each patient was treated within 4 weeks. The clinical outcome was evaluated twice: after allocation and after treatment. Adverse events were recorded on the case report form (CRF) at any time during treatment*.

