### Randomization

Eligible patients were allocated, in a 1:1 ratio were randomly assigned to the experimental group or the control group, following the randomization principle, which employs block randomization to generate random-number sequence using the SPSS, and an independent statistician who did not participate in the treatment and result evaluation was responsible for processing the results. Meanwhile, we also prepared sealed opaque envelopes with group information strips in these envelopes, which was hidden until the informed consent was obtained.

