### Blinding

Due to the limitations of this protocol and the nature of acupuncture treatment, the acupuncturists participating in this trial could not be blinded to the assignments, the patients were blinded. Patients were informed that they will be randomized to receive one of two effective interventions after registration. Every patient knew the type of treatment they received, but they did not know another type. Each patient's acupuncture intervention was carried out in a separate personal space and at different times to avoid communication between patients. The distribution of patient groups by data managers and statisticians was not clear. Experts, data managers, and statisticians were not allowed to communicate with others about patients' treatment, so as to improve the accuracy of test indicators and ensure the effectiveness of interventions and the objectivity and reliability of the evaluation. The blind method was made public after the statistical analysis was completed.

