### Sample Size

The purpose of this study was to evaluate the efficacy of FA in the treatment of ULPSS. According to previous research and clinical experience, the effective rate of TA is about 65%, and the effective rate of FA will probably reach 85% (31). The significance test level is 0.05, and the test power is 0.9. The sample size is calculated by using:

$$\begin{array}{l} N=P\left(1-P\right){\left(\frac{\alpha +\beta }{\delta }\right)}^{2} \end{array}$$

where N is the required sample size for each treatment group, and the sample size of each group is equal. When α is 0.05 and β is 0.1, the normal distribution quantile table shows that:

$$\begin{array}{l} Z_{\text{α}/2}=1:645 \end{array}$$

and

$$\begin{array}{l} Z_{\text{β}/2}=1:282 \end{array}$$

P_0_ and P_1_ represent the original curative effect and the expected curative effect, 65 and 85%, respectively. δ represents the mean difference between two groups, by substituting the above parameters and values into the formulas, 49 cases will be needed for each group. Accounting for a 10% expulsion rate, the final estimated sample size will be about 54 cases per group (108 in total).

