### Statistical Analysis

After all the experimental data are verified to be correct, SPSS19.0 statistical software is used for statistical analysis. Classified variables will be analyzed using Pearson's χ^2^ test or Fisher's exact test, and continuous variables will be evaluated using Student's *t*-test or an appropriate non-parametric method. The statistical results are measured by the mean ± standard deviation (SD; *x* ± s); when comparing within or between groups, tests for normality and homogeneity of variance are performed prior to data analysis for each group. If the data satisfy normal distribution and homogeneity of variance, the *t*-test will be used for comparisons between two groups, and the least significant different (LSD) or Student-Newman-Keuls (SNK) method will be used for multiple comparisons. Instead, the rank-sum test will be used for non-normality or non-uniformity of variance. Set the test level as 0.05, *p* < 0.05, and the difference was statistically significant.

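### The interim stopping rule names two comparator groups in a two-arm trial and gives the lead investigator comparative results while recruitment is still open

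*Protocol article*

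**What the plan says.** All references are to the protocol article.

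- **Design.** Trial Design and Setting says the investigators "randomly divided them into 2 groups, with 54 patients in each group". Randomization says patients "in a 1:1 ratio were randomly assigned to the experimental group or the control group". Interventions describes FA against TA, each added to routine rehabilitation. No third arm appears in any of these sections.
- **Interim look.** Quality Control: "When the total number of samples collected reaches 54, statistical analysis will be carried out".
- **Who decides.** The next sentence: "The lead investigator will obtain these interim results and decide whether to continue the trial".
- **Criterion.** The sentence after that begins "If the efficacy of the experimental group is lower than that of the other two groups in the results of interim data" and ends by committing the team to stop. It gives no endpoint and no size of difference.
- **Blinding.** Acupuncturists are unblinded. Patients are described as blinded, and data managers and statisticians as unaware of group allocation. On opening the blind: "The blind method was made public after the statistical analysis was completed".
- **Test level.** Sample Size: "The significance test level is 0.05, and the test power is 0.9". Statistical Analysis: "Set the test level as 0.05". Neither section gives a separate interim level.

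**The concern.** This rule decides whether the trial continues, and three things about it do not fit the rest of the document.

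1. It compares FA with a pair of groups when there is one comparator. Statistical Analysis also names LSD and SNK multiple comparisons, which have no role between two arms, so the text may partly reflect a design with more groups.
2. It can only be operated if someone knows which arm is FA and how it compares with the other. That information goes to the lead investigator with about half the patients still to be recruited. The setting is a single centre with unblinded acupuncturists and rater-scored outcomes. Expectations formed at the interim could affect recruitment, treatment or scoring in the second half.
3. One sentence leaves continuation to the lead investigator's decision and the next prescribes a stop. Two readers could act differently on the same interim result, and the choice of endpoint is also open: Sample Size plans on an effective rate, while Primary Outcomes names the MAS.

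**Working it through.** **Step 1. The plan's own figures, to fix the timing of the look.** Sample Size gives rates of 65% (TA) and 85% (FA), quantiles 1.645 and 1.282, and 10% loss. The printed formula with P = 0.65 gives 0.65 × 0.35 × [(1.645 + 1.282)/0.20]² = 0.2275 × 214.2 = 48.7, hence 49 per group. Then 49 × 1.10 = 53.9, hence 54 per group and 108 in total. The stated sizes reproduce. (Whether that formula suits a two-group comparison is a separate matter.) The look at 54 patients falls at 54/108 = 0.5 of the information, about 27 per arm under 1:1 allocation.

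**Step 2. Number of groups.** Trial Design and Setting, Randomization and Interventions all give one experimental and one control group. Quality Control needs two other groups. The only workable reading is FA against TA, and the steps below use it.

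**Step 3. How often the repaired rule stops.** Quality Control names no endpoint, so I assume the effective rate from Sample Size and read lower as a numerically lower count of responders. With X_FA and X_TA independent binomial, n = 27 each, P(stop) = P(X_FA < X_TA):

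| True rates, FA v TA | P(stop) |
|---|---|
| 65% v 65% | 0.443 |
| 75% v 65% | 0.169 |
| 85% v 65% (planned) | 0.028 |

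**Step 4. Cost in power.** The loss is P(Z₁ < 0 and Z₂ > 1.96), where Z₁ and Z₂ are the interim and final statistics with correlation √0.5, at 54 per arm and two-sided 0.05. At 85% v 65% the standard error is √[(0.85 × 0.15 + 0.65 × 0.35)/54] = √(0.355/54) = 0.081. The expected Z₂ is 0.20/0.081 = 2.47, the expected Z₁ is 2.47 × √0.5 = 1.74, and the loss is about 0.4 points. At 75% v 65% it is about 0.2 points. Simulating the two-proportion test (1,000,000 runs) at 85% v 65% gives 68.2% power without the look and 68.0% with it. Most trials that the rule stops would not have reached significance.

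**Step 5. Type I error under the written rule.** With the downward stop only, the chance of a false FA-favouring result is P(Z₁ ≥ 0 and Z₂ > 1.96) = 0.0247, against 0.025 without a look. There is no inflation.

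**Step 6. What a benefit stop would do, if one were allowed.** Testing at two-sided 0.05 at half information and again at the end gives 1 − P(|Z₁| < 1.96 and |Z₂| < 1.96) = 0.083. No sentence in the document provides for such a stop.

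**Step 7. Access set beside blinding.** Quality Control sends the interim results to the lead investigator. The criterion requires FA to be identified and compared. Blinding opens the blind only once the statistical analysis is complete. The two fit together only if interim results are exempt or the lead investigator was never meant to be blind, and the document says neither.

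**The case against.** The comparator wording can be called a slip, since with one control arm the intended comparison is obvious. That is fair as far as meaning goes, and Steps 3 to 5 rely on it. But a rule that can end the trial should not need repair by its reader.

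It can also be said that the Blinding section never lists the lead investigator among those kept blind, and that nothing says interim results reach the outcome assessors. That stands: the conflict is inferred, not explicit. It is still a firm inference, because the criterion cannot be applied without comparative results.

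The 44% stopping rate sounds alarming, but it arises when FA has no advantage, which is when a futility look should stop often. At the planned effect the rate is 3% and almost no power is lost. This stands too, so the percentages describe the rule's behaviour and are not in themselves evidence of harm.

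A reader might go further and infer that keeping the final test at 0.05 is an error and that the true error rate is 8.3%. The documents do not support this. The only stop they state is for worse efficacy, which leaves the FA-favouring error at 0.0247. The 8.3% needs a benefit stop that appears nowhere. Not excluding one is silence in a condensed article, and interim alpha detail commonly sits in a full protocol or analysis plan that is not shown.

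**Conclusion.** The point holds in limited form. It is certain that the stopping rule refers to more comparator groups than the trial has, that it names no endpoint, and that its discretionary and mandatory sentences are not reconciled. It is a firm inference that the lead investigator would hold between-arm results mid-recruitment, which must be reconciled with the Blinding section.

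The numerical consequences are modest. The stopping probabilities of 44%, 17% and 3% assume the effective-rate endpoint, 27 per arm, and a stop on the bare sign of the difference; on the MAS they would differ. On the same assumptions the power loss is under 0.5 points and the final 0.05 level is correct. The reason to act is that the rule is ambiguous and exposes interim results, not that it damages the error rates.

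**What to change.** Amend Quality Control before the look at 54 patients:

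1. Replace the reference to two other groups with the single TA group.
2. Name one endpoint for the comparison.
3. State whether the stop binds or is advisory, and align the two sentences.
4. State that the look is for futility or harm only, with no stop for benefit, so that the final 0.05 stands. If a benefit stop is wanted after all, the two looks need adjusted levels, for example 0.0052 and 0.0480 (O'Brien-Fleming).
5. Have the comparison made by someone independent of treatment and assessment. Randomization already mentions an independent statistician, but Blinding says statisticians do not know the allocation, so the text must say who sees the allocation at the interim and keep that person apart from the blinded work.
6. Pass only continue or stop to the lead investigator, and add a matching sentence to Blinding.

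A conditional-power threshold on the MAS is not proposed, because the document gives no planned MAS effect or standard deviation from which to compute it.

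The cost is amendment wording and the assignment of one independent person. The small downside is that the lead investigator loses sight of the interim results.

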## Discussion

Spasticity is one of the most common causes of physical disability in the world. Patients often recover their lower limb function faster in rehabilitation training, while the upper extremity function, especially the fine motor function of the hand, usually recovers for a long time, which seriously affects the daily life of patients (40). In recent years, the achievements of modern rehabilitation medicine and acupuncture mechanism have made acupuncture and moxibustion more effective in treating ULPSS, improving clinical symptoms of ULPSS, preventing cerebrovascular diseases, and reducing the incidence rate of PSS, but some problems still need to be solved. The purpose of this study was to evaluate the efficacy and safety of FA in the treatment of ULPSS.

### Selection of Acupoint Prescription

In this study, FA was selected, and its acupoint selection was also exquisite. It mainly includes PC7, LI4, and functional point. PC7 (41) is an important point of the pericardium meridian (PC). It is on the palmar side of the forearm, between the palmar long tendon and the radial wrist flexor tendon. The tissues involved after rapid acupuncture include palmar long tendon and radial wrist flexor tendon, internal and external cutaneous nerves, median nerve trunk, and interosseous nerve of forearm, which can relax the contracture hand fingers to a state of no flexion, passive activity, and no resistance for several hours. LI4 (42) is the original point of the large intestine meridian (LI), and the LI reaches the head. Stimulating this point can make the Jing Qi (essence) reach the head, regulate the health with the camp, calm Yin and Yang, and calm the brain and mind. Acupuncture emphasizes that acupuncture “leaves acupoints and does not leave meridians” (43). Acupuncture combines Yin and Yang, dredges meridians, dredges Jing Qi, regulates blood and Qi, and connects multiple meridians. The penetrating needling of LI4 to SI3 can directly alleviate the finger flexor spasticity and indirectly excite and stretch the finger extensor tendon. By repeatedly stimulating the flexor tendon, it can alleviate the spasticity and improve the finger dysfunction. In this state, the use of functional point electrical stimulation can quickly improve the overall function of the upper limb. Functional points 1 and 2 are two new points found in the process of clinical treatment. The treatment method we used for these two points is called “FA.” The body surface positioning of functional points 1 and 2 is not fixed. Functional point 1 is roughly equivalent to the position of Zhoumiu (LI12) of the Large Intestine meridian (LI). There is a radial neuromuscular junction under it. Stimulating this point can produce finger extension and wrist dorsum flexion. In actual operation, when the electroacupuncture instrument is connected, the adjustment of the needle tip direction to produce the maximum passive action with the minimum current intensity is the key to the FA. At this time, the electroacupuncture instrument and the connected electroacupuncture can achieve the function of functional electrical stimulation, but its effect is better than the functional electrical stimulation with the surface electrode as the contact point; Functional point 2 is roughly equivalent to the position of Waiguan (SJ5) point of the triple energizer (TE) meridian. As an auxiliary point, it is connected to the positive pole of the electroacupuncture instrument. It can be seen from the above that this is an innovative acupuncture method with a unique acupoint selection. It adopts the combination of traditional acupoints and anatomical position, the combination of traditional needling method and through needling and fast needling, and the combination of traditional needling feeling and strong needling feeling. There are few clinical studies. This study selects TA as the control, selects the commonly used acupoints of ULS from data mining technology for comparison, which can intuitively feel the clinical efficacy of this acupuncture method.

### The Combination of Subjective and Objective Outcome Measures

In addition to the scale evaluation selected in this study, we also adopted the evaluation methods, such as surface electromyography (sEMG) and electrophysiological measurement (H-reflex), and adopted a combination of subjective and objective methods to reduce the impact of a series of human interventions on the experimental results and make the study more convincing (44).

One important limitation of our study is an acupuncture trial, it is impossible to perform a double-blind procedure. In order to reduce this bias, each group of patients will receive treatment at different times in different rooms, and communication between each group of patients is prohibited. In addition, all acupuncturists participating in this study will receive unified training, strictly standardize acupuncture operation, and eliminate the error of the study to the greatest extent.

In conclusion, this report describes a randomized controlled trial that systematically evaluates the rehabilitation effect of FA on patients with ULPSS. To observe the clinical effect of functional acupuncture on ULPSS, and to determine whether FA can effectively improve the ULS and improve the extremity motor function and self-care ability of patients after stroke. This study not only provides a new idea for the clinical treatment of ULPSS but also provides effective experimental support and a theoretical basis for the clinic.

### Trial Status

The recruitment of patients for this study began on 1 September 2021, and this study is ongoing. Protocol version number and date: V2.0, 1 September 2021. The recruitment of patients is expected to be completed in May 2022.

## Ethics Statement

The studies involving human participants were reviewed and approved by the Ethics Committee of the First Affiliated Hospital of Henan University of Chinese Medicine. The patients/participants provided their written informed consent to participate in this study.

## Abbreviations

ULS: Upper limb spasticity
ULPSS: upper limb post-stroke spasticity
PSS: post-stroke spasticity
FA: Functional Acupuncture
TA: Traditional Acupuncture
BoNT-A: botulinum toxin A
SPIRIT, Standard Protocol Items: Recommendations for Interventional Trials
CT: Computed tomography
MRI: Magnetic resonance imaging
PASS: Power analysis and sample size
SPSS: Statistical Package for the Social Sciences
RMS: Root mean square
MAS: Modified Ashworth Scale
FMA-UE: Fugl–Meyer Assessment for Upper Extremity
MBI: Modified Barthel Index
CRFs: Case report forms
sEMG: Surface electromyography
H-reflex: electrophysiological measurement.
